### Sample analysis

Based on retrospective data from our institution in the same surgical population (mean duration until first defecation 4.82 days, SD of 0.82 days), a power analysis was performed using duration of return of GI function as the primary variable. For a calculated sample size of 18 patients in each group (36 patients in total) the study is designed to have an 90% power (β = 0.10) for the Wilcoxon/Mann–Whitney test to detect a difference of 1 day between the groups (Ringerfundin® and G5-K solution) at a two-sided significance level of 5% (α = 0.05) assuming an SD of 1 day (G Power Version 3.1.5., Kiel and Duesseldorf, Germany). This decrease of 1 day is considered clinically relevant. Assuming a drop out of 20%, 22 patients per group will be recruited.

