### Statistics

Data will be analyzed by the research team in collaboration with a medically versed biostatistician. There will be no interim analysis.

Statistical analysis will be conducted on an intention-to-treat basis. Data distribution will be tested by Q-Q plots. Normally distributed data will be presented as mean and standard deviation (SD), skewed data as median and range, and dichotome data as number and percentage. Comparing related and unrelated continuous samples, the paired and unpaired *t*-tests, respectively, will be used for normally distributed data and the Wilcoxon signed rank test and Mann–Whitney *U*-test, respectively for skewed data. Differences in proportions will be analyzed using the Fisher’s exact test, and risk ratio with associated 95% confidence interval (CI). For the analysis of the primary endpoint, we will use the unpaired Student *t*-test with associated 95% CI. In addition, a multiple logistic regression analysis will be carried out, including the randomization groups and all clinically relevant variables (age, ASA scores, Charlson comorbidity score, Glasgow prognostic score, postoperative fluid balance). A two-sided *P* value of less than 0.05 will be considered significant.

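### The stated 90% power does not follow from the stated inputs: 18 per group gives 83% for the planned t-test and about 80 to 81% for the Mann–Whitney test with normal data

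*Protocol article*

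**What the plan says.** The sample size paragraph (Protocol article, Sample analysis) fixes every input except the shape of the distribution.

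- Size and power: "For a calculated sample size of 18 patients in each group (36 patients in total) the study is designed to have an 90% power".
- Test and effect: the calculation is "for the Wilcoxon/Mann–Whitney test to detect a difference of 1 day between the groups". On the size of the effect it adds: "This decrease of 1 day is considered clinically relevant".
- Level and spread: "at a two-sided significance level of 5% (α = 0.05) assuming an SD of 1 day". The retrospective SD in the same paragraph is 0.82 days, so 1 day is a deliberately wider planning value.
- Dropout: "Assuming a drop out of 20%, 22 patients per group will be recruited".

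The Statistics section repeats the level, "A two-sided *P* value of less than 0.05 will be considered significant", and names a different test for the primary endpoint: "For the analysis of the primary endpoint, we will use the unpaired Student *t*-test with associated 95% CI".

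**The concern.** A 1-day difference with an SD of 1 day is a standardized difference of 1. For that effect at a two-sided 5% level, 18 per group is well short of the usual requirement for 90% power. The trial has no interim analysis, so this paragraph is the only justification of its size. If the true power is nearer 80%, the accepted risk of missing a 1-day benefit is nearly double the published 10%. A non-significant result would then be read as stronger evidence against that benefit than the design supports.

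**Working it through.** **Inputs (Sample analysis and Statistics):** difference 1 day; SD 1 day; d = 1/1 = 1; two-sided α = 0.05; equal groups of n = 18; 20% dropout; 22 recruited per group.

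**Can the plan's own figure be reproduced?** Not from these inputs, as the next two steps show.

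**t-test.** Power is P(|T| > t_crit), where T follows a noncentral t distribution with 2n − 2 degrees of freedom and noncentrality d√(n/2). For n = 18 there are 34 degrees of freedom, the noncentrality is √9 = 3.0 and t_crit = 2.032. Power = **83.0%**. Even the cruder normal approximation gives only 85.1%.

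**Mann–Whitney test, normal data.** The efficiency method replaces n by n × 3/π. For n = 18 that is 18 × 0.955 = 17.2, and power = **81.2%**. Lehmann's method gives 80.6%. Simulation with exact critical values (40,000 replicates) gives 80.1%. With the minimum relative efficiency of 0.864, power is 76.9%.

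**Size needed for 90% (two-sided 5%, d = 1).** t-test: 23 per group. Mann–Whitney with normal data: 23 (Lehmann) or 24 (efficiency method). Mann–Whitney at minimum efficiency: 26.

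**Which inputs do give about 90% at 18?**

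| Route | Power at 18 | Conflict with the text |
|---|---|---|
| One-sided 5% t-test, SD 1 | 90.2% | level is two-sided, stated twice |
| Two-sided Mann–Whitney, minimum efficiency, SD 0.82 | 90.8% | SD is fixed at 1 |
| Two-sided Mann–Whitney, Laplace data, SD 1 (Lehmann) | 90.3% | distribution not stated |

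Which of these was used, if any, cannot be told from the article.

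**Dropout.** Multiplying gives 18 × 1.2 = 21.6, rounded up to the stated 22. To keep 18 after losing 20%, one divides: 18/0.8 = 22.5, so 23. With 22 recruited, 22 × 0.8 = 17.6 remain.

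**Power of the design as planned (d = 1, two-sided 5%, normal data):**

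| Evaluable per group | t-test | Mann–Whitney |
|---|---|---|
| 17.6 (22 less 20%) | 82% | 80% |
| 18 | 83.0% | 80–81% |
| 22 (no loss) | 90.0% | 88–89% |

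**Detectable difference.** At 18 per group with SD 1, 90% power is reached at 1.11 days (t-test) or 1.14 days (Mann–Whitney, efficiency method), against the 1 day called clinically relevant.

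**The case against.** Four arguments can be made for the plan.

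1. **The rank test needs a distribution, and the article gives none.** With heavy-tailed (Laplace) data, Lehmann's method gives 90.3% at 18 and simulation 89.5%, without contradicting any printed input. This stands as a possibility, so the 80 to 81% for Mann–Whitney must be read as conditional on normality. It does not rescue the trial's power: the primary analysis is the t-test, which still has about 83% under Laplace data.

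2. **The SD may be smaller.** At the retrospective 0.82 days (d = 1/0.82), 18 per group gives 94.4% (t-test) or 93.4% (Mann–Whitney, normal data). That softens the practical consequence. But the plan chose 1 day as its planning value and attached the 90% to it.

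3. **44 patients will be recruited, and losses may be few.** The endpoint is recorded in hospital until it occurs, and analysis is by intention to treat, so the full 20% may not be lost. With all 22 per group evaluable, the t-test has 90.0%. This is fair, but it means the stated power is met only if the plan's own dropout assumption turns out wrong.

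4. **The planned 95% confidence interval will show whether 1 day is excluded.** True, and it limits over-reading of a null result. It does not correct the published power.

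The dropout slip alone is minor: one patient per group, and less than one percentage point of t-test power (83.0% against 82.1%).

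**Conclusion.** The power statement is wrong as written. On the stated difference, SD, level and group size, power falls short of 90% by 7 points for the planned t-test and by 9 to 10 points for the Mann–Whitney test. The type II error is 1.7 to 2 times the stated 10%. The t-test figure barely depends on the distribution: about 83% under normal, logistic and Laplace data alike. The Mann–Whitney figure assumes normal data. Both take the SD as 1 day, and the shortfall disappears if the true SD is 0.82. The dropout error is real but small; it matters only because the extra patients are meant to protect 18 per group and do not quite do so.

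**What to change.** Rewrite the sample size paragraph and keep 44 patients. Suggested text:

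*With 22 evaluable patients per group, a difference of 1 day, an SD of 1 day and a two-sided 5% level, power is 90% for the unpaired t-test and 88% for the Mann–Whitney test (normal data). If 20% drop out, leaving 17 to 18 per group, power is about 82% and 80% respectively.*

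Correct the dropout step to n/(1 − 0.20). Give the power for the test used in the primary analysis. If a one-sided level, the SD of 0.82 or a non-normal distribution lay behind the 18, say so. The power at SD 0.82 can be added as a sensitivity figure.

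The cost is one corrected paragraph and a less favorable headline power, with no added patients. If 90% after 20% dropout is in fact wanted, the price is 23/0.8 = 28.75, so 29 per group (t-test), or 24/0.8 = 30 per group (Mann–Whitney): 58 to 60 patients in place of 44.

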### Assessment of safety

The methods used to measure plasma and urine samples are those established at our hospital and used in everyday clinical practice. Both intravenous solutions will be provided by the pharmacy of the University Hospital Bern. Both solutions are routinely used at our institution (Department of Anesthesia and Department of Intensive Care Medicine).

### Reporting of adverse events

Follow-up will be guaranteed because every patient included in the trial will receive daily visits from the urologist in charge and will have blood samples taken. In addition, all patients will be continuously monitored during POD 1 to 5, as they will be on the intermediate care unit.

The principal investigator ([name]) will monitor the patients for any adverse events (AEs), which are defined as any unfavorable and unintended sign (including abnormal laboratory results), symptom, or disease temporally associated with the use of the randomized infusions. This will be documented on the CRF and immediately communicated to the principal investigator.

Serious AEs (SAEs) are defined as any untoward medical occurrence at any dose that results in death, or is life-threatening (i.e. patient was at risk of death at the time of the event), requires inpatient hospitalization or prolongation of existing hospitalization, or results in persistent or significant disability/incapacity. All treatment related to SAEs will be recorded and reported to the local ethics committee. An investigation will be conducted, and a report on the findings generated before the study can be resumed, in accordance with the Good Clinical Practice Guidelines of the Declaration of Helsinki.

### Duration and timeline

The annual caseload of cystectomy is around 100 in our institution per year. We expect to recruit our participants within 18 months. The study protocol was designed and approval from the local ethics committee obtained in 2013, and participants will be recruited during 2014 and 2015.

## Discussion

The present study will improve knowledge on the use of perioperative crystalloid solutions in patients with bladder cancer undergoing radical cystectomy with urinary diversion. This information should produce a basis on which to develop strategies that aim to prevent perioperative morbidity such as delayed return of the GI function and postoperative renal dysfunction.

The primary outcome of this study is the return of GI function, which is a cornerstone of the postoperative management of patients after major abdominal surgery. Delayed return of GI function is one of the major reasons for prolonged hospitalization time. The potential implications of our results are important. Accelerating the return of GI function will inevitably shorten hospitalization time and thus reduce the cost of hospital expenditure.

We expect by using the G5-K solution, which does not contain chloride anions, to achieve not only a near-zero water balance, as we already demonstrated in a previous RCT, but also a near-zero salt balance after radical cystectomy with urinary diversion [1]. In contrast we expect the patients in the Ringerfundin® group to be at higher risk of having a positive fluid and salt balance. This non-accumulation of salts and water in the G5-K solution group is expected to result in an earlier return of the GI function. Lobo *et al*. already showed that a positive salt and water balance after colonic resection delayed the return of GI function and resulted in longer hospitalization time. In addition, perioperative chloride loading is known to impair urinary output, and to induce metabolic acidosis and even hyperkalemia in patients with preoperative renal dysfunction.

## Conclusion

In conclusion, this trial is an investigator-initiated, pragmatic, randomized clinical trial to test the hypothesis that administration of glucose-rich balanced crystalloid solution containing potassium can accelerate the return of GI function. In addition, this study will also determine the effect of this solution on renal function after radical cystectomy with urinary diversion.

## Trial status

The trial is ongoing.

## Abbreviations

ASA: American Society of Anesthesiologists; BNP: Brain natriuretic peptide; CI: confidence interval; CRF: case report form; GI: gastrointestinal; MAP: Mean arterial pressure; NGAL: Neutrophil gelatinase-associated lipocalin; PRBC: Packed red blood cells; POD: postoperative day; RCT: Randomized clinical trial; RIFLE: risk, injury, failure, loss, end-stage renal disease; SD: standard deviation.
